## 6. Procedures Involved

Study participants will complete a web-based survey reporting reproductive health needs, fertility-related outcomes, and pursuit of a fertility status assessment. Clinical characteristics will be abstracted from participant's medical records. Both the survey data and clinical data will be entered and stored in Children's Healthcare of Atlanta REDCap (<http://project-redcap.org/>), which is a secure, web-based application for building and managing online surveys and databases. Participating sites will only have access to their own site's data; the coordinating center (Emory/CHOA) will have access to all data across sites. REDCap is HIPAA compliant and designed to support data capture for research studies, providing an intuitive interface for validated data entry;

audit trails for tracking data manipulation and export procedures; automated export procedures for seamless data downloads to statistical software packages; and procedures for importing data from external sources A subset of participants will be invited to participate in a qualitative interview. Interviews will be audio-recorded and transcribed verbatim. Audio recordings will be stored in a password-protected secure folder on the Emory server and destroyed after data analysis is complete. Figure 2. Presents the mixed methods procedural diagram for this study.

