### **Data to be collected**

**Medical Record Data:** **Clinical Characteristics**, including cancer diagnosis, date of diagnosis, number of cancer survivor clinical encounters, hormonal laboratory assessments, prior hormone treatment, gonadotoxic therapeutic exposures [alkylating and heavy metal chemotherapy, gonadotoxic radiation], surgeries, history of hematopoietic cell transplant, and date of cancer treatment completion will be abstracted from participant's medical records by the site CRC using an adapted version of the COG Summary of Cancer Treatment Template.

[figure not shown]

**Quantitative Survey Data:** Participants will be invited to complete a web-based REDCap survey assessing sociodemographic and developmental factors, reproductive factors (knowledge, concerns, behaviors, and health needs), psychological factors, and history of FSA. The survey instrument is included with this protocol.

**Sociodemographic factors** include gender identity, race/ethnicity, religion, education level, household income, insurance and relationship status, and items are consistent with national surveys of young adults. **Developmental factors** will be assessed through the lens of emerging adulthood using The Markers of Adulthood (MoA) scale, which characterizes the attainment of behavioral milestones among emerging adults, and the IDEA-8 characterizes a self-perceived state of transition (e.g., feeling in-between); both scales have been used in large multi-site studies with emerging adults across diverse populations.

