sites who are unable to use email recruitment, will contact patients by phone. The site research coordinator will describe the purpose of the study and patients who are interested will be emailed a link to the REDCap survey or will be provided with a web address to access the survey. Patients who are unable or choose not to complete the survey online will be mailed a paper copy, with a self-addressed stamped envelope to return to the coordinating site. The study research coordinator will enter participant responses from paper surveys into the REDCap database.

Mail: Sites may recruit participants by mailing a letter describing the study and inviting participation.

In-person: Finally, if eligible patients have scheduled clinical visits within the oncology center, the research coordinator may recruit patients during the clinical encounter.

Recruitment methods will be tracked by the site research coordinators. Recruitment approaches may vary across sites to align with institutional processes. Patients may be contacted up to 5 times total for recruitment, which may be a combination of email/My Chart, phone call, or letter.

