### **Data Management**

All data will be collected and stored through the password protected and secure REDCap database; audio recordings for qualitative interviews will be stored in password protected files on the secure Emory University server. At each participating site, access to data will be restricted to approved study team members and study-related files will be stored in password protected files. If a participant completes the survey using paper and pencil, the hard copy of the survey will be stored at the participating site in a locked drawer and data will be entered into REDCap by the approved site CRC.

Data will be coded whenever possible through the use of assigned study identification numbers. Upon dissemination of results, no identifiable data will be included in presentations or publications. All study team members will maintain certification in human subjects research through the Collaborative Institutional Training Initiative (CITI) program. To protect privacy, participants will be encouraged to complete the web-based REDCap survey in a private area. Similarly, qualitative interviews will be scheduled during a time when participants can have privacy.

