## **25. Multi-Site Research When Emory is the Lead Site**

This study will recruit eligible participants from three external sites. Collaborative site research teams will consist of a site PI and clinical research coordinator. The site PI will be responsible for obtaining site IRB approval, identifying eligible participants at their site, supervising the site research coordinator, and overseeing site activities. The clinical research coordinator will be responsible for recruiting participants, completing the Treatment Summary form for participants, and communicating with the coordinating center.

The PI will monitor recruitment across sites through several strategies. Regular communication will occur between the study PI and the site PIs to discuss any challenges in identifying or recruiting eligible patients. The site study teams will complete a bi-weekly recruitment report detailing progress and noting any problems with recruitment. If needed, changes will be made to the recruitment process to meet the needs of each participating site (e.g., relying more heavily on phone or mail recruitment if email recruitment is not successful).

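### Chart abstraction is not protected from knowledge of the FSA answer, and the two rules for mailed paper surveys conflict at the three external sites

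*Protocol*

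**What the plan says.** **Access.** Section 6 (Procedures Involved) states: "Both the survey data and clinical data will be entered and stored in Children's Healthcare of Atlanta REDCap". It then says "Participating sites will only have access to their own site's data", with the coordinating center seeing all sites. Section 19 (Data Management) adds that at each site "access to data will be restricted to approved study team members". No distinction is drawn between survey responses and clinical forms.

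**Abstraction.** Section 6 (Data to be collected) has the clinical characteristics "abstracted from participant's medical records by the site CRC using an adapted version of the COG Summary of Cancer Treatment Template". The list covers diagnosis, dates, gonadotoxic exposures, surgery and transplant, and also hormonal laboratory assessments, prior hormone treatment and the number of survivor-clinic encounters. Section 25 confirms the combined role: "The clinical research coordinator will be responsible for recruiting participants, completing the Treatment Summary form for participants".

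**Outcome.** Section 19 (Aim 1) defines the primary outcome as a yes to the survey item on having met a reproductive specialist. Aim 1.3 regresses it on clinical and other covariates.

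**Paper surveys.** Section 14 (Phone Call) says patients who do not complete the survey online "will be mailed a paper copy, with a self-addressed stamped envelope to return to the coordinating site", and that the study research coordinator enters the answers. Section 19 (Data Management) says that for paper completion "the hard copy of the survey will be stored at the participating site in a locked drawer and data will be entered into REDCap". It assigns this data entry to the site's own coordinator.

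**The concern.** In Aim 1.3 the chart variables are exposures and the self-reported FSA is the outcome. If the person reading the chart knows that a participant reported an FSA, that person may search harder for endocrine tests, hormone treatment or related visits. An exposure recorded more completely in recipients than in non-recipients gives a spurious association even where none exists. Aim 1.3 also lets bivariable associations guide backward selection, so a modest artefact can affect which factors stay in the final model and feed the planned intervention. It cannot be corrected once the data are collected.

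The paper-survey rules matter for the same reason: one routes the outcome away from the external sites, the other puts it in the abstracting role's hands.

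**Working it through.** **1. Who can know the outcome when abstracting?**

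| Step | Protocol source | What follows |
|---|---|---|
| Survey and clinical data in one REDCap | Section 6 | Same system |
| Each site sees its own data | Section 6 | Survey answers not excepted |
| Site coordinator abstracts and completes the Treatment Summary | Sections 6 and 25 | Abstractor is the site coordinator |
| Site coordinator keys paper surveys | Section 19, Data Management | Same role handles the FSA answer |
| Masking, or abstraction before survey | Not stated | No protection |

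For paper surveys under Section 19 the exposure to the outcome is explicit. For web surveys access is allowed by the site rule, but no text says that the coordinator reads the answers.

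**2. Paper rules side by side.**

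| | Section 14 | Section 19 |
|---|---|---|
| Scope | Paper copies mailed out | Any paper completion |
| Destination | Coordinating site | Participating site |
| Entered by | Study research coordinator | Approved site coordinator |

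At Emory the coordinating and participating sites coincide. At the three external sites in Section 23 the destinations differ for mailed forms, and no forwarding step is described.

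**3. The plan's design figure, used here only as a yardstick.** Inputs from Section 19 (Power Analysis): 70.4% v 50% exposed, 65 v 260 respondents, 4 sites, ICC 0.01, two-sided unpooled Z-test at 0.05.

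- Odds ratio: (0.704/0.296)/(0.5/0.5) = 2.38, stated as 2.4.
- Design effects, 1 + (m − 1) × 0.01: m = 65/4 = 16.25 gives 1.1525; m = 260/4 = 65 gives 1.64.
- SE = √(0.704 × 0.296 × 1.1525/65 + 0.5 × 0.5 × 1.64/260) = 0.0726.
- Power = Φ(0.204/0.0726 − 1.96) = 80.2%, against the stated 80%.

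The power figure reproduces, and the present point does not depend on it.

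**4. Size of a possible artefact.** The documents give no abstraction sensitivities, so those below are assumptions. Take a true odds ratio of 1.0, specificity of 100%, true exposure π in both groups, and sensitivities s₁ (FSA) and s₀ (no FSA). The apparent odds ratio is [πs₁/(1 − πs₁)] / [πs₀/(1 − πs₀)].

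| s₁ v s₀ | Gap | π = 30% | π = 50% |
|---|---|---|---|
| 92% v 90% | 2 points | 1.03 | 1.04 |
| 95% v 90% | 5 points | 1.08 | 1.11 |
| 100% v 90% | 10 points | 1.16 | 1.22 |
| 95% v 80% | 15 points | 1.26 | 1.36 |

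Example, last row at 50%: (0.475/0.525)/(0.400/0.600) = 1.36.

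With 65 v 260 and the same test and ICC, a true null would be rejected at the nominal 5% level about 5% of the time for the 2-point gap, 7% to 10% for the 10-point gap, and 10% to 16% for the 15-point gap (lower figure π = 30%, higher π = 50%).

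**The case against.** The strongest reply is that the protocol nowhere says the abstractor is unblinded. The Section 6 access sentence is about separation between sites, and form-level permissions may be set in the database build. Web completion is the preferred route and paper the fallback. Section 14 has records examined before recruitment to verify eligibility, so part of the treatment history is reviewed before any answer exists. Most abstracted items are record facts on a structured template. The chart can itself show an FSA: the preliminary data in Section 3 came from medical records and found 13% with one documented. Section 3 also says an FSA can include hormone tests, so some association with hormonal laboratory assessments is structural and masking would not remove it.

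Much of this stands, and it limits the point. A reader might infer that outcome-aware abstraction is an established bias, or that coordinators abstract after reading the survey. The documents support neither: the order of abstraction and survey is not fixed, and reading of web answers is permitted but not described. Nor do they support a bias in a direction the study seeks, since Aim 1.3 states no directional hypothesis for chart variables.

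What the reply does not answer is Section 19, which puts paper answers in the hands of the role that abstracts.

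On the paper rules, a reader might conclude that they can never both be followed. That goes too far: Section 14 covers mailed copies, and storage at the site fits forms completed in person. But Section 19 is not limited to in-person forms, so the conflict remains for mailed surveys at the external sites.

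**Conclusion.** The point holds as a lack of protection, not as a demonstrated bias. The stated rules allow the abstracting role to know the primary outcome, and for paper surveys handled under Section 19 they ensure that this role handles it. Differential ascertainment is plausible but modest, and mainly concerns hormonal laboratory assessments, prior hormone treatment and encounter counts; diagnosis, dates, chemotherapy, radiation and transplant should be little affected.

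At 50% exposure the apparent odds ratio under no association runs from about 1.04 to 1.36 for gaps of 2 to 15 points. This rests wholly on assumed sensitivities and on recipients' status being known and acted on. It is small beside the design value of 2.4, but could influence variable selection.

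The conflict between Sections 14 and 19 for mailed surveys at the three external sites is plain from the text and needs no assumption. Both deserve correction because the remedy is cheap and later repair is not possible.

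**What to change.** - **Sections 6 and 19 (Data Management):** state that site coordinators see consent, survey completion status and the abstraction form, but not survey responses; or require abstraction to be finished before the survey is opened. Section 22 sends e-consenting participants straight from consent into the survey, so restricted access is the more practical choice there. Because that consent is the first page of the REDCap survey, the restriction must leave the consent record visible to the site.
- **Sections 14 and 19:** reconcile them so that mailed paper surveys are returned to, entered at and stored at the coordinating center. Forward paper forms completed in person there sealed.
- **Lead site:** Emory is also the coordinating center and plans 100 of the 325 participants, so a permission setting for external sites does not cover it. Abstract before the survey is opened where possible.

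The cost is a REDCap permission setting and a few sentences. Survey queries move to the coordinating center, which already has access to all data. The change reduces unblinding but does not remove it, because the chart may document an FSA.

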### **Data to be collected**

**Medical Record Data:** **Clinical Characteristics**, including cancer diagnosis, date of diagnosis, number of cancer survivor clinical encounters, hormonal laboratory assessments, prior hormone treatment, gonadotoxic therapeutic exposures [alkylating and heavy metal chemotherapy, gonadotoxic radiation], surgeries, history of hematopoietic cell transplant, and date of cancer treatment completion will be abstracted from participant's medical records by the site CRC using an adapted version of the COG Summary of Cancer Treatment Template.

[figure not shown]

**Quantitative Survey Data:** Participants will be invited to complete a web-based REDCap survey assessing sociodemographic and developmental factors, reproductive factors (knowledge, concerns, behaviors, and health needs), psychological factors, and history of FSA. The survey instrument is included with this protocol.

**Sociodemographic factors** include gender identity, race/ethnicity, religion, education level, household income, insurance and relationship status, and items are consistent with national surveys of young adults. **Developmental factors** will be assessed through the lens of emerging adulthood using The Markers of Adulthood (MoA) scale, which characterizes the attainment of behavioral milestones among emerging adults, and the IDEA-8 characterizes a self-perceived state of transition (e.g., feeling in-between); both scales have been used in large multi-site studies with emerging adults across diverse populations.

**Reproductive knowledge** will be assessed using an overall score of correct answers (0-12) to items regarding cancer and fertility preservation. Gaps in knowledge will be assessed through self-reported knowledge level (item response options include none, a little, a lot) regarding fertility after cancer (e.g., impact of cancer treatment on fertility, knowledge of infertility testing and treatment). Survivors will also report their perceived risk for infertility (none, low, moderate, high) and how they perceive their risk for infertility compared with peers who have not had cancer. The modified **Reproductive Concerns Scale (mRCS)** consists of 7 items with 3 subscales measuring participant's fertility-related concerns, illness concerns related to pregnancy/parenthood, and information-seeking regarding reproductive health. The mRCS has been validated among adolescent and young adult survivors of childhood cancer. **Fertility-related distress** will be assessed using three domains of the Fertility Problem Inventory (FPI), a 27-item multidimensional scale measuring infertility stress, impact on social dimensions, and importance of parenthood and the Couple's Relationship Concern subscale from the Reproductive Concerns After Cancer scale; higher scores indicate increased distress. **Reproductive health behaviors** will include pregnancy and birth history, contraceptive history and current use, and sexual behaviors. **Reproductive health needs** will be assessed through items identifying unmet educational needs, desire for contraceptive counseling, and interest in FSA.

Psychological factors will also be assessed. **Decisional conflict** will be measured using the Decisional Conflict Scale, which measures four dimensions of decision making: information, values, support, and uncertainty; each subscale is scored 0-100 with higher scores indicating greater decisional conflict. The effective decision subscale will be used to measure **decisional satisfaction** among participants who have received an FSA; scores range from 0-100 with lower scores representing a good decision.

**Fertility Status Assessment** will be assessed with the item "*Have you ever met with a reproductive specialist to assess your fertility? (e.g. reproductive endocrinologist or a fertility specialist)*". Participants who respond 'Yes' will also be asked details about this assessment (e.g., testing, results, discussion of infertility treatment options). Participants who respond 'No' or 'I don't know' will be asked their level of interest (Likert scale 1 [not at all interested] to 5 [very interested]), and perceived barriers to not receiving an FSA (e.g., lack of awareness, cost).

**Qualitative Interview Data:** Participants for the qualitative interviews will be identified through analysis of the quantitative survey if they (1) indicated on the survey that they are willing to take part in a qualitative interview and (2) responded to the survey item assessing receipt of an FSA. The interviewers for this study are English-speaking, therefore only participants who speak English will be invited to take part in the qualitative interview. We will use a qualitative descriptive approach, which is low-inference and seeks to describe the experiences of participants through their words and

experiences. In line with this approach, we will use maximum variation sampling, which is a preferred method for descriptive qualitative inquiry, to increase the representativeness of the sample in relation to the population being studied by recruiting participants across sites and those who have and have not received an FSA.

Interviews will be conducted until data saturation is reached; we estimate the sample size to be 32 participants, (8 at each participating site). We will try to have approximately equal number of participants who have and have not received FSA at each site, however, some sites may have higher success rates testing patients, therefore stratification of patients by FSA status may not be possible at the site level. However, we will ensure overall there are approximately 16 participants who have received an FSA and 16 who have not received an FSA.

The interview guide will be developed and informed by descriptive results from the quantitative survey. Planned interview questions include a discussion of factors that influenced participants' decision to pursue or not pursue FSA, satisfaction with that decision, barriers encountered when accessing FSA, and resources needed to support survivors who are interested in FSA.

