**Cancer survivors are interested in fertility status assessment.** A fertility status assessment (FSA) for females can include medical history, assessment of menstrual-cycle specific laboratory hormones and antral follicle count, and discussion of ovarian reserve and fertility potential, generally through a consult with a fertility specialist (e.g., reproductive endocrinologist). While assessment of gonadal function is sometimes completed in a cancer survivor clinic, these tests are not definitive, and estimation of future fertility can be difficult. The gold standard for fertility assessment is an antral follicle count, which is best completed by a reproductive specialist who can provide a perspective beyond that of treatment-related risk. Among survivors at risk for infertility, FSA is recommended in accordance with national guidelines among interested patients. In a sample of 98 young adult cancer survivors, 71% of females reported interest in a FSA and over half were interested in further reproductive health information delivered via a website or follow-up visit. Females who are at risk for premature ovarian insufficiency may have a window for fertility preservation, therefore timely FSA provides an opportunity for discussing options for fertility preservation, and potentially intervening in a timely fashion in order to improve preservation outcomes. However, little is known regarding factors related to receipt of an FSA in female survivors of childhood cancer.

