### **19. Data Analysis, Management and Confidentiality**

**Aim 1. Data Analysis:** Statistical analysis will be performed using SAS v.9.4 (Cary, NC) and CRAN R v.3.6 (Vienna, Austria), and statistical significance will be evaluated at the 0.05 threshold. Initial analyses will be undertaken to inspect data for errors, inconsistencies, and incomplete information. Data anomalies and outliers will be examined and corrected or removed if necessary. Descriptive statistics for sociodemographic and developmental factors, and clinical characteristics will be presented as means and standard deviations or medians and interquartile ranges for continuous variables and frequencies/percentages for categorical variables.

The primary outcome of Aim 1 is receipt of an FSA, defined as an answer of 'yes' to the survey item *"Have you ever met with a reproductive specialist to assess your fertility?"*. Based on prior research, and clinical experiences at the participating sites, we anticipate 20% of the sample will report receipt of an FSA.

**Aim 1.1. and Aim 1.2:** Descriptive statistics for reproductive health knowledge, values, health behaviors, and prevalence of reproductive health needs, as well as decisional conflict and fertility-related psychological distress, will be examined using means and standard deviations, medians and interquartile ranges, or percentages and frequencies, as appropriate. For the primary outcome variable (i.e., “yes” for an FSA), frequency and percentage will be calculated with a 95% confidence interval. Hypothesis tests between FSA cohorts (i.e., yes versus no) will be made using two-sample t-tests and chi-square tests of independence (or non-parametric equivalents such as Wilcoxon rank-sum and Fisher’s exact tests); moreover, effect sizes will be calculated to determine standardized differences in exposure values between the FSA cohorts and interpreted using Cohen’s *d* criteria: small (0.2), moderate (0.5), and large (0.8).

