**Aim 1.3:** To assess associations between model parameters describing sociodemographic, clinical, reproductive health needs and decisional conflict (covariates) and receipt of an FSA (outcome), we will employ bivariable and multivariable binary logistic regression models. For all logistic regression models, model parameters for sociodemographic, clinical, reproductive health needs and decisional conflict will be treated as fixed effects and study sites will be evaluated as random effects, where appropriate, to account for potential differences in outcome variability between the study locations (i.e., clustering); moreover, fit statistics will be gauged (i.e., AIC, BIC, log-likelihood) for all regressions and appropriate assumptions will be checked, such as linearity in covariates and normality of residuals. Final multivariable results will be guided by the bivariable associations and determined using backward selection procedures, as well as any relevant clinician input. Estimates from these models will be presented as odds ratios for receipt of an FSA with 95% confidence intervals and p-values.

**Power Analysis:** The primary endpoint for this study will be receipt of an FSA. Based on insights from the literature, and our own clinical experiences, we anticipate 20% (n=65) of the sample will have received an FSA and 260 respondents will have not. These sample sizes, which will be obtained by sampling 4 study sites, achieve 80% statistical power to detect an odds ratio of 2.4 for discrete exposures. This odds ratio corresponds to 70.4% of respondents in the FSA group having the exposure, versus 50% of respondents in the non-FSA group having the exposure (i.e., a percent difference of 20.4%). Power was calculated in PASS v.14.0.8 (Kaysville, UT), with a two-sided un-pooled Z-test, an intra-cluster correlation (ICC) of 0.01, and a statistical significance level of 0.05.

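### Hormone laboratory tests can be part of an FSA, yet as clinical characteristics with no stated timing they fall among the covariates for FSA receipt, so a test from the specialist work-up can appear to predict that visit

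*Protocol*

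**What the plan says.** Four places in the protocol bear on this point.

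- **Section 3, Background** (paragraph on interest in fertility status assessment): an FSA "can include medical history, assessment of menstrual-cycle specific laboratory hormones and antral follicle count, and discussion of ovarian reserve and fertility potential", and is obtained "generally through a consult with a fertility specialist (e.g., reproductive endocrinologist". The same paragraph adds: "While assessment of gonadal function is sometimes completed in a cancer survivor clinic, these tests are not definitive".
- **Section 6, Data to be collected, Medical Record Data**: the items abstracted under the label of clinical characteristics include "hormonal laboratory assessments, prior hormone treatment, gonadotoxic therapeutic exposures". Dates are listed for diagnosis and for the end of cancer treatment. None is listed for the hormone tests, and neither is the clinic that ordered them.
- **Section 6, Fertility Status Assessment, and section 19, Aim 1**: "The primary outcome of Aim 1 is receipt of an FSA", taken as a yes to a survey item on whether the respondent has ever seen a reproductive specialist about her fertility. The examples of follow-up detail for those who answer yes cover testing, results and treatment discussion, but not when the visit took place.
- **Section 19, Aim 1.3**: the stated task is "To assess associations between model parameters describing sociodemographic, clinical, reproductive health needs and decisional conflict (covariates) and receipt of an FSA (outcome"), using bivariable and multivariable logistic models. The final model is to be guided by the bivariable results, backward selection and clinician input.

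**The concern.** Aim 1.3 is meant to identify factors related to receipt of an FSA, and section 2 says that the results will shape a later decision-support intervention. A covariate is useful for that only if it precedes the outcome. Hormone tests may precede a specialist visit, for instance when a survivor-clinic result prompts a referral. They may equally be ordered at the visit or after it. The protocol states nothing that separates the two, and it places the tests in the class of variables used to explain the visit.

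The selection rule adds to the problem. Screening on bivariable association and then eliminating backward tends to keep whatever is most strongly associated with the outcome, and a by-product of the outcome is a natural candidate. Once retained, it can take up association that belongs to real factors and push them out of the model. A consequence of the assessment would then be reported as one of its determinants.

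**Working it through.** **1. The plan's own figure.** Section 19 plans for 65 FSA recipients and 260 non-recipients at 4 sites, exposure of 70.4% against 50%, ICC 0.01, a two-sided unpooled Z-test and alpha 0.05.

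- Odds ratio: (0.704/0.296) / (0.50/0.50) = 2.38, stated as 2.4.
- Design effect 1 + (m − 1) × ICC, with 4 clusters per group: m = 65/4 = 16.25 gives 1.1525, and m = 260/4 = 65 gives 1.64.
- SE = √(0.704 × 0.296/65 × 1.1525 + 0.50 × 0.50/260 × 1.64) = 0.0726.
- Power = Φ(0.204/0.0726 − 1.96) = 80.2%.

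The stated 80% reproduces with that reading of the ICC, so no stated figure is wrong. The planned effect serves below only as a yardstick.

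**2. Odds ratio produced by the overlap alone.** The documents give no testing rates, so these inputs are assumptions:

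- s0: the share of women with a hormone test on record for reasons unrelated to an FSA, the same in recipients and non-recipients (no true effect).
- a: among recipients who would otherwise have no test on record, the share who acquire one through the FSA.

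The share of recipients with a test on record is then s1 = s0 + (1 − s0) × a. The odds ratio for having a test on record is [s1/(1 − s1)] / [s0/(1 − s0)].

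| s0 | a = 10% | a = 30% | a = 50% |
|---|---|---|---|
| 30% | s1 = 37%, OR 1.37 | s1 = 51%, OR 2.43 | s1 = 65%, OR 4.33 |
| 50% | s1 = 55%, OR 1.22 | s1 = 65%, OR 1.86 | s1 = 75%, OR 3.00 |

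If specialist tests never reach the abstracted record, a = 0 and the odds ratio is 1. Rarer background testing makes the distortion larger: s0 = 20% with a = 50% gives s1 = 60% and (0.60/0.40)/(0.20/0.80) = 6.0.

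**3. Would it pass the bivariable screen?** Take the middle case, s0 = 30% and a = 30%, so 51% against 30%. With the design effects of step 1:

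- SE = √(0.51 × 0.49/65 × 1.1525 + 0.30 × 0.70/260 × 1.64) = 0.0759.
- Φ(0.21/0.0759 − 1.96) = Φ(0.81) = 0.79.

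In that case a variable with no predictive effect would be significant at the 0.05 level about 79% of the time, much as a real factor of the planned size would be.

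**The case against.** The strongest reply is that the overlap is inferred. Section 6 is a data-collection list, and Aim 1.3 speaks of clinical factors without naming hormone tests. The covariate list and its coding (test done, or hormone level) could be settled in a statistical analysis plan that is not at hand, and clinician input could remove the variable. The abstraction form and the survey are not shown either and may record dates. It is also unknown whether tests ordered by an outside specialist reach the abstracted record.

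Much of this stands. It rules out saying that the tests are certainly undated, or that the odds ratio will certainly be large. Where background testing is common and few tests arise through the FSA, the inflation is slight (1.22 at s0 = 50%, a = 10%). But section 6 gives clinical characteristics a defined content that includes the tests, and nothing in section 19 takes them out. An analysis plan could exclude them, but it cannot restore a date that was never collected.

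A reader might go further and infer that the outcome contradicts the protocol's own definition, because women tested only in a survivor clinic count as non-recipients. The text does not support that. Section 3 says what an FSA can include, ties it generally to a specialist consultation and explains why clinic tests do not suffice. Sections 6 and 19 then use the specialist visit consistently. At most, the non-recipient group is mixed.

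A reader might also calculate that the planned odds ratio falls from 2.38 to 1.57 if half of the non-recipients were clinic-tested and resembled recipients. That treats the 50% exposure rate as belonging to never-tested women, whereas section 19 gives it for the whole non-FSA group. It also assumes full resemblance.

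**Conclusion.** The point holds for the predictor. As written, the protocol places a possible component of the FSA among the covariates for receipt of the FSA, with no stated rule on timing or source and a selection method that would tend to keep it. Tests done at or after the specialist visit can inflate their own odds ratio and may displace real factors in the Aim 1.3 model.

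The size is unknown. It is about 1.2 to 4.3 with no true effect, for a test-on-record indicator, if background testing is 30% to 50% and 10% to 50% of otherwise untested recipients gain a record through the FSA. It is nil if specialist tests do not reach the record. The point does not extend to the outcome definition, the make-up of the comparison group or the power calculation.

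**What to change.** State in section 19, Aim 1.3, one of the following:

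1. Hormonal laboratory assessments are not candidate covariates for receipt of an FSA. This costs one sentence. The loss is a possible real predictor, namely an earlier clinic result that prompts a referral.
2. Only tests dated before the first specialist visit are used. This keeps that predictor, but needs lab dates in the abstraction and one survey question on the date of the first specialist visit, if these are not already collected.

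Keep the specialist-visit outcome and the sample size as they are.

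As an option, record where each test was ordered and report the share of non-recipients with a clinic hormone test on record. A sensitivity comparison of recipients with non-recipients who have no recorded test could be added. It should carry the caution that the absence of a record does not prove that a woman was never tested. Its comparison group would be smaller than 260, so precision would be somewhat lower in that analysis only.
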